#### Primary outcomes

Fasting plasma glucose (FPG): fasting is defined as no caloric intake for at least 8 h2-h plasma glucose (2-hPG) level after 75-g oral glucose tolerance test (OGTT): the test should be performed as described by the WHO, using a glucose load containing the equivalent of 75 g anhydrous glucose dissolved in waterGlycosylated hemoglobin (HbA_1c_)

All the primary outcomes will be tested on visit 1 (within 1 week before the study), visit 25 (after 24 weeks), and visit 26 (after 48 weeks).

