**Methods/design:**

An RCT will be implemented in this study, using a72-week study period (24 weeks for the intervention and 48 weeks for follow-up). Participants will be recruited from the Fifth Affiliated Hospital of Guangzhou Medical University in China. Eighty participants will be randomized to the treatment group (acupuncture plus herbal medicine and health education) or the control group (health education only), 40 participants in each. People included in this study must have been diagnosed with prediabetes using Western medicine criteria. The endpoint indices include the incidence of diabetes mellitus and the reversion rate. The primary outcome is fasting plasma glucose (FPG) level, 2-h plasma glucose (2-hPG) level after a 75-g oral glucose tolerance test (OGTT), and glycosylated hemoglobin (HbA_1c_) level. Secondary outcomes include the following: Body Mass Index (BMI); hemorheology, including shear rates of whole-blood viscosity and plasma viscosity. Safety indices include hepatic (ALT, AST) and renal function (BUN, Cr) and records of adverse events, including diarrhoea, colds, pharyngitis, and sleep disorders. Quality control will be implemented, including quality control of the laboratory, researchers, participants, investigational drugs, data and documents, occurrence of bias, supervision, among others, according to uniform standard operating procedures (SOPs) which have been established by the Good Clinical Practice (GCP) office of the Fifth Affiliated Hospital of Guangzhou Medical University.

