### Randomization

We will use ResMan Research Manager (RRMS) (http://www.medresman.org/login.aspx) to manage the trial data. Randomization of the trial will be completed by RRMS. According to a random sequence table generated by RRMS, participants who satisfy the inclusion criteria will be randomly allocated into one of the two groups in a ratio of 1:1. Unique identification codes and randomization numbers will be generated for each participant in RRMS.

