### Sample size

Given the difficulty determining an adequate sample size due to the lack of sufficient preliminary studies, we adopted a pilot study design with 40 participants per group, considering the limited research funds.

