### Statistical analysis plan

#### Analysis parameters

All parameters will be analyzed using SPSS 19.0 software.

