#### Statistical analysis method

Student’s *t* test will be used for group comparison (treatment group versus control group) on primary outcomes and secondary outcomes. the chi-square test will be used for comparing the endpoint events (occurrence of type-2 diabetes and blood glucose change to normal).

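### Three primary outcomes at two post-baseline visits, with no principal marker, primary visit, success rule or multiplicity control

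*Protocol article*

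**What the plan says.** The abstract speaks of one primary outcome and then lists three: "The primary outcome is fasting plasma glucose (FPG) level, 2-h plasma glucose (2-hPG) level", followed by HbA1c. The Primary outcomes section lists the same three markers and gives the measurement schedule: "All the primary outcomes will be tested on visit 1 (within 1 week before the study), visit 25 (after 24 weeks". A further measurement of all three is scheduled at visit 26. The Discussion again treats all three as primary.

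The article has its own Statistical analysis plan section. Under Statistical analysis method, a Student's t "test will be used for group comparison (treatment group versus control group) on primary outcomes and secondary outcomes". That sentence names no visit, no order among the markers and no adjustment. A chi-square test is assigned to two further endpoint events, onset of type-2 diabetes and return to normal glucose. The Analysis parameters section gives only the software ("All parameters will be analyzed using SPSS 19.0 software"). No significance level appears anywhere in the article.

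The Objectives section covers both short-term and long-term effectiveness. The Sample size section says "we adopted a pilot study design with 40 participants per group, considering the limited research funds".

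**The concern.** As written, the plan does not define a positive trial. Three markers and two post-baseline visits give up to six group comparisons that could be reported as a primary result, with two endpoint events beside them.

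Discordant results are foreseeable. The Diagnostic criteria admit a participant on any one of the three markers, so many may enter abnormal on one and normal on the others. One significant marker and two null ones is a realistic result, and nothing in the protocol says whether that is success.

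The Abstract's stated aim is to evaluate efficacy and safety. The Background expects the laboratory outcomes to establish the glucose-lowering effect of the treatment. If the result that supports that claim can be picked after the data are seen, the claim does not carry the error rate of a single test.

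**Working it through.** **Inputs from the article.** Three primary markers; two post-baseline visits (25 and 26); t test between groups; 40 per group; 1:1 allocation.

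**Inputs assumed, because the article does not give them.** (a) Two-sided 5% per test. (b) Any one significant result counts as success. (c) For the six-test figures, formal t tests at both visits. (d) Correlations of 0 to 0.7 between markers and 0.5 to 0.7 between visits.

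The plan states no error rate, power or effect size, so there is no figure of its own to reproduce.

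**Step 1: independent tests, as an upper reference.** Familywise error = 1 − (1 − 0.05)^k.
- One visit, k = 3: 1 − 0.95³ = 14.3%.
- Two visits, k = 6: 1 − 0.95⁶ = 26.5%.

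**Step 2: correlated tests.** Two-sample t tests were simulated with 40 per arm and no treatment effect, 40,000 runs per setting. The Monte Carlo standard error is about √(0.2 × 0.8 / 40,000) = 0.2 percentage points.

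| Correlation between markers | Correlation between visits | One visit, 3 tests | Both visits, 6 tests | Both visits, favouring treatment only |
|---|---|---|---|---|
| 0 | 0.5 | 14.3% | 25.0% | 13.0% |
| 0 | 0.7 | 14.3% | 23.3% | 12.1% |
| 0.5 | 0.5 | 12.8% | 22.1% | 11.1% |
| 0.5 | 0.7 | 12.8% | 20.5% | 10.1% |
| 0.7 | 0.5 | 11.0% | 19.1% | 9.4% |
| 0.7 | 0.7 | 11.0% | 17.8% | 8.9% |

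The two-sided columns compare with a nominal 5%, the last column with 2.5%. Over a wider grid (0 to 0.7 between markers, 0 to 0.8 between visits) the six-test figure runs from 16.7% to 26.6%.

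**Step 3: the opposite success rule.** If all three markers must be significant at one fixed visit, the chance that all three are falsely significant cannot exceed the chance for any one of them. The error is then at most 5%, with no inflation.

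**Step 4: the price of control.** Holm over three markers sets the first threshold at 0.05/3 = 0.0167. With 40 per arm, a standardised difference of 0.634 has 80% power at 0.05 by the noncentral t distribution. At 0.0167 the same difference has 65%. The normal approximation agrees: a difference of 0.626 gives Φ(0.626 × √20 − 1.960) = 80% and Φ(0.626 × √20 − 2.394) = 66%.

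**The case against.** A reader might infer that the protocol commits to six unadjusted t tests and so has a false-positive risk of 18-25% in place of 5%. The article does not support that as a statement of fact. In the Primary outcomes section, being tested means the laboratory assay: the sentence includes baseline, and the same verb is used for the safety tests and BMI. The t test sentence names no visit. No significance level is stated, and nothing says that one significant result is enough. The two-sided figure also counts false results in favour of control, which are not the harm of concern. All of this stands, and it is why the figures are conditional.

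A second objection is that this is a condensed article and adjustment may be set out in an analysis plan not shown. That is fair for the detail of the adjustment, and silence does not prove that none is planned. It is weaker for the choice of principal marker, visit and success rule, which belong in the protocol. The authors do fix a visit where they want one: the Additional indicators section calculates incidence and reversion at visit 26 only. The Objectives section, with its short-term and long-term aims, also makes it natural to read both visits as efficacy comparisons.

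Third, a pilot need not control familywise error, and the Sample size section explains that choice ("Given the difficulty determining an adequate sample size due to the lack of sufficient preliminary studies"). This softens the point. It does not remove it, because the Abstract and Background set out to evaluate efficacy and demonstrate a glucose-lowering effect.

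**Conclusion.** The concern holds as an undefined primary analysis. The protocol has three primary markers at two post-baseline visits, compared by plain t tests, and no stated rule for what counts as success.

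The size depends on the rule that is eventually used. With any one result at two-sided 5% counting, the risk is about 11-14% for one visit and 18-25% for both. For results favouring treatment at either visit it is about 9-13% against 2.5%. With all three markers required at one fixed visit there is no inflation. The significance level, the any-one rule, testing at both visits and the correlations are all assumptions.

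This should be corrected. The Trial status section says the trial had not started at submission, so the rule could be set before any outcome is seen.

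**What to change.** In the Primary outcomes and Statistical analysis method sections, name one primary visit, for example visit 25 at the end of the intervention. State the significance level and adopt one of these rules:
- test the three markers at that visit with Holm at a family two-sided 5%;
- name one marker as primary and make the other two secondary;
- require all three markers to be significant, each at 5%.

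Report the other visit as a secondary long-term comparison with 95% confidence intervals, so the long-term objective is kept. State that the two endpoint events carry no confirmatory claim. Viscosity needs no relabelling, as it is already secondary. BMI, incidence and reversion are already listed as additional indicators.

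**Cost.** The change is one of wording, but under Management of protocols a modification needs Ethics Committee approval, and the trial is already registered, so the record should be made to match. Under Holm the smallest p value must reach 0.0167. Power for a single marker at that step falls from 80% to about 65% with 40 per arm, and the later steps are less strict. Requiring all three markers avoids the stricter threshold but also costs power, because every marker must succeed. Naming one marker keeps the full 5% for it, but the other two can no longer carry the claim.

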#### Secondary outcomes

Middle shear rates of whole-blood viscosity (30/S)Low shear rates of whole-blood viscosity (10/S)Low shear rates of whole-blood viscosity (1/S)Plasma viscosity

Hemorheology, including shear rates of whole-blood viscosity and plasma viscosity, will be tested by capillary method by the same researcher.

All the secondary outcomes will be tested on visit 1 (within 1 week before the study), visit 25 (after 24 weeks), and visit 26 (after 48 weeks).

#### Safety indices

Alanine aminotransferase (ALT) levelsAspartate aminotransferase (AST) levelsBlood urea nitrogen (BUN) levelsCreatinine (Cr) levels

All the safety indices will be tested on visit 1 (within 1 week before the study) and visit 25 (after 24 weeks).

#### Additional indicators

Body Mass Index (BMI): BMI = weight (kg)/square of height (m^2^). The weight and height of participants will be measured by the same equipment in the Medical Examination Centre of the Fifth Affiliated Hospital of Guangzhou Medical UniversityIncidence of type-2 diabetes mellitus

Calculated using the following formula:$$ \mathrm{Incidence}\ \mathrm{of}\ \mathrm{diabetes}\ \mathrm{mellitus} = \mathrm{Cases}\ \mathrm{of}\ \mathrm{diabetes}\ \mathrm{mellitus}/\mathrm{Total}\ \mathrm{cases}\ \mathrm{of}\ \mathrm{each}\ \mathrm{group} \times 100\% $$
Reversion rates of FBG, 2-hPG after 75-g OGTT, and HbA_1c_ after 48 weeks of follow-up;

Calculated using the following formula:$$ \mathrm{Reversion}\ \mathrm{rate} = \mathrm{Cases}\ \mathrm{o}\mathrm{f}\ \mathrm{blood}\ \mathrm{glucose}\ \mathrm{t}\mathrm{hat}\ \mathrm{have}\ \mathrm{returned}\ \mathrm{t}\mathrm{o}\ \mathrm{normal}/\mathrm{cases}\ \mathrm{o}\mathrm{f}\ \mathrm{each}\ \mathrm{group} \times 100\% $$

BMI will be tested on visit 1 (within 1 week before the study), visit 25 (after 24 weeks), and visit 26 (after 48 weeks).

Incidence of type-2 diabetes mellitus, reversion rates of FBG, 2-hPG after 75-g OGTT, and HbA_1c_ will be calculated only on visit 26 (after 48 weeks).

### Adverse event monitoring

#### Reporting of adverse events

Participants will be required to immediately report adverse events (AEs) to researchers when they occur. Researchers will also ensure that the study is proceeding as intended every 8 days when participants visit them at the hospital.

When serious adverse events (SAEs) occur, researchers must complete an SAE Form and immediately report the event to the project leader and the Ethics Committee of the Fifth Affiliated Hospital of Guangzhou Medical University. The event should also be reported to the China Food and Drug Administration (CFDA) within 24 h.

#### Documentation of adverse events

The AE Report Form must be completed according to the actual circumstances. Some additional information, including the event time, severity, duration, measure adopted, and the outcome should be noted as well.

#### Relationship between adverse event and study treatments

The researchers will assess the relationship between the AE and the treatments being studied with the following criteria:Whether the suspected adverse reaction appears after treatment administrationWhether the suspected adverse reaction belongs to the known adverse reactions of the investigated drugWhether the suspected adverse reaction disappeared or was mitigated after discontinuation of treatmentWhether the same reaction occurred again after resuming the investigated drugWhether the suspected adverse reaction cannot be explained by the participant’s diseases or consumption of the combination of drugs

#### Relationship between adverse events and changes in symptoms

This trial differs from other trials, as the formulas prescribed to the participants will be adjusted according to the changes in symptoms caused by receiving the last formula. Therefore, AEs can be useful to the Chinese doctor for adjusting the prescribed formulas.

#### Criteria for the evaluation of safety

As an adverse reaction could not be the criterion of safety in this trial, the safety of the TCM interventions will be assessed by hepatic and renal function as follows:Safe without any significant changes in hepatic or renal functionRelatively safe with less than 20% changes in hepatic and renal functionTermination of the interventions due to more than 20% changes in hepatic and renal function

### Statistical analysis plan

#### Analysis parameters

All parameters will be analyzed using SPSS 19.0 software.

#### Statistical analysis method

Student’s *t* test will be used for group comparison (treatment group versus control group) on primary outcomes and secondary outcomes. the chi-square test will be used for comparing the endpoint events (occurrence of type-2 diabetes and blood glucose change to normal).

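### The t test named for the primary and secondary outcomes has no baseline term, although all of them are measured at visit 1; it is valid but less precise than ANCOVA

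*Protocol article*

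**What the plan says.** The Statistical analysis method section names one method for continuous outcomes: Student's t test "will be used for group comparison (treatment group versus control group) on primary outcomes and secondary outcomes". It mentions no covariate, change score or model. The endpoint events (onset of type-2 diabetes, return to normal glucose) go to a chi-square test.

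The outcomes under the t test all have a baseline value. Under Primary outcomes: "All the primary outcomes will be tested on visit 1 (within 1 week before the study), visit 25 (after 24 weeks"), and again at visit 26. Under Secondary outcomes, for the viscosities: "All the secondary outcomes will be tested on visit 1 (within 1 week before the study), visit 25 (after 24 weeks"), and again at visit 26.

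The abstract describes the primary outcomes as levels: "The primary outcome is fasting plasma glucose (FPG) level, 2-h plasma glucose (2-hPG) level after a 75-g oral glucose tolerance test (OGTT") and the HbA1c level.

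The Sample size section gives no power calculation. It refers to too few preliminary studies and says "we adopted a pilot study design with 40 participants per group, considering the limited research funds". Under Randomization, participants are "randomly allocated into one of the two groups in a ratio of 1:1".

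**The concern.** In a randomized comparison of a continuous outcome, the baseline value of the same variable is often the best single predictor of the follow-up value. A t test on follow-up levels leaves that information unused. A t test on changes uses it with a fixed weight of one, which is generally not the best weight.

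Precision matters in this trial because the sample size was set by funds and not by a target power, while the Objectives section sets out to evaluate effectiveness. With 40 per arm, the standard error of a chance difference between arms at visit 1 is √(2/40) = 0.22 SD. The t test's own standard error already allows for that variation, so the test is not misled by it. Adjustment removes the part that baseline explains, and the interval becomes narrower.

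**Working it through.** **Inputs from the protocol.** 40 per arm (Sample size); 1:1 allocation (Randomization); Student's t test with no baseline term (Statistical analysis method); measurements at visits 1, 25 and 26 (Primary outcomes, Secondary outcomes).

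**Inputs assumed, because the protocol does not give them.** Two-sided 5% level; a true difference of 0.5 SD for illustration; a correlation ρ between the visit-1 and follow-up values from 0.2 to 0.7; equal SDs at the two visits.

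**The plan's own figure.** The 40 per arm cannot be reproduced, since no significance level, power, effect or SD is stated for it.

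**Variance of the estimated difference, relative to a t test on follow-up levels**

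- t test on levels: 1
- t test on changes: 2(1 − ρ)
- ANCOVA on the visit-1 value: 1 − ρ²

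**Detectable difference.** The t test on levels with 40 per arm detects 0.634 SD with 80% power (noncentral t). ANCOVA detects 0.634 × √(1 − ρ²); at ρ = 0.6 this is 0.634 × 0.8 = 0.507 SD.

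**Power for 0.5 SD.** The noncentrality is 0.5 × √(40/2) / √(1 − ρ²) = 2.236 / √(1 − ρ²), with 78 degrees of freedom for the t test (ρ set to 0) and 77 for ANCOVA. The equivalent unadjusted sample size per arm is 40 / (1 − ρ²).

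| Analysis | Variance saved | Detectable difference, 80% power | Power for 0.5 SD | Equivalent n per arm |
|---|---|---|---|---|
| t test on levels | – | 0.63 SD | 60% | 40 |
| ANCOVA, ρ = 0.2 | 4% | 0.62 SD | 62% | 42 |
| ANCOVA, ρ = 0.3 | 9% | 0.60 SD | 64% | 44 |
| ANCOVA, ρ = 0.5 | 25% | 0.55 SD | 72% | 53 |
| ANCOVA, ρ = 0.6 | 36% | 0.51 SD | 79% | 62 |
| ANCOVA, ρ = 0.7 | 49% | 0.45 SD | 87% | 78 |

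**Check by simulation** (10,000 trials for each ρ, 40 per arm, 0.5 SD). At ρ = 0.3, 0.5 and 0.7 the power was 60%, 59% and 60% for the t test on levels; 46%, 60% and 81% for the t test on changes; and 63%, 72% and 87% for ANCOVA.

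**If changes are tested.** The ANCOVA variance divided by the change-score variance is (1 − ρ²) / [2(1 − ρ)] = (1 + ρ)/2. This is 0.60, 0.65, 0.75, 0.80 and 0.85 at the five correlations, and below 1 for every ρ below 1. When ρ is below 0.5, a t test on changes is also less precise than one on levels, because 2(1 − ρ) then exceeds 1.

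**With dropout.** The Dropout criteria section expects less than 15%. If the full 15% were lost, 34 per arm would remain. Power for 0.5 SD is then 53% unadjusted, and 55%, 57%, 65%, 72% and 81% with ANCOVA at the five correlations.

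**The case against.** **The t test is valid.** This stands. Randomization keeps the comparison unbiased and the type I error at its nominal level. A reader might infer that chance imbalance at visit 1 biases the result. It does not, because the t test's standard error already covers it. The point is one of efficiency.

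**The protocol does not say what is tested.** This also stands. The outcomes are described as levels and no change score appears, so levels is the natural reading, but it is an inference. A flat statement that the plan discards the baseline would go too far. The conclusion does not depend on the reading, since ANCOVA is more precise than either t test once ρ is large enough to repay one degree of freedom.

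**The correlation is unknown.** This stands too. A reader might argue that because people enter on any one of three indices, baseline values vary widely and much of the follow-up variance must be predictable. That does not follow: spread at baseline does not establish correlation with a value many weeks later. The upper diagnostic limits and the exclusion of known diabetes may lower the correlation, and so may a treatment adjusted every 8 days.

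**Adjustment may not be the only gain available.** A reader might see it as the only free source of power in a trial sized by funds. The documents do not show that; two follow-up visits are also available.

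**Carried-forward values complicate ANCOVA.** The full analysis set uses last observation carried forward. For a participant with no follow-up measurement, the outcome would equal the covariate, which would raise the apparent correlation. This is a fair caution about implementation, but the same imputed values would also enter the t test.

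**A fuller plan may hold these details.** Possibly, but the article names the test. That is a stated choice and not a silence, and an adjusted analysis elsewhere would depart from it.

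**Conclusion.** The point holds as a near-costless improvement in precision, not as an error of validity. A t test without a baseline term is named for outcomes that all have a visit-1 value, and ANCOVA would use that value better on either reading of the text.

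The size depends on a correlation that the protocol does not give. Against a t test on levels, the variance saved runs from 4% at ρ = 0.2 to 49% at ρ = 0.7, and power for 0.5 SD moves from 60% to between 62% and 87%. At ρ of 0.2 or below the gain is negligible. These figures assume a two-sided 5% level, 40 per arm with complete data, and equal SDs at the two visits. The chi-square comparisons of endpoint events are not affected.

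**What to change.** In the Statistical analysis method section, replace the t test for the primary and secondary outcomes by ANCOVA. Regress the visit-25 value, and separately the visit-26 value, on arm and the visit-1 value of the same variable. Report the adjusted mean difference with its 95% CI at each visit. A baseline-adjusted mixed model using both follow-up visits is an acceptable alternative. Leave the chi-square tests as they are.

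State alongside this how participants with no follow-up measurement enter the model, given the carry-forward rule under Analysis of datasets.

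The cost is one degree of freedom and a change of wording. No new data are needed. Trial status says that the study had not started at submission, so the change could be prespecified without sight of results.
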